**Figure 2 F2:**
[figure not shown]
Royal Australian College of General Practitioners (RACGP) dosage guidelines.

**Table 1 T1:** NRT options for participants to select at baseline (8-week supply) and follow-up (4-week supply)

		NRT types supplied	High-dose pack	Low-dose pack
Baseline supply (8-week supply)	Option 1—cNRT	Patch, gum and lozenge	2 boxes of 25 mg patches* 4 boxes of 4 mg gum 4 packs of 4 mg lozenges	2 boxes of 25 mg patches* 4 boxes of 2 mg gum 4 packs of 2 mg lozenges
	Option 2—cNRT	Patch, mouth spray and gum	2 boxes of 25 mg patches 4 packs of mouth spray 4 boxes of 4 mg gum	2 boxes of 25 mg patches* 4 packs of mouth spray 4 boxes of 2 mg gum
	Option 3—cNRT	Patch, mouth spray and lozenge	2 boxes of 25 mg patches 4 packs of mouth spray 4 packs of 4 mg lozenges	2 boxes of 25 mg patches* 4 packs of mouth spray 4 packs of 2 mg lozenges
	Option 4—oral NRT only	Gum, mouth spray and lozenge	3 boxes of 4 mg gum 2 packs of mouth spray 3 packs of 4 mg lozenges	3 boxes of 2 mg gum 2 packs of mouth spray 3 packs of 2 mg lozenges
Follow-up supply (4-week supply)	Patches		1 box of 25 mg patches	4 boxes of 15 mg patches
	AND/OR		AND/OR	AND/OR
	Oral NRT (Participants select up to 4 packs in total)		A selection of the following (up to 4 packs in total): 1 pack of 4 mg lozenges 1 pack of 4 mg gum 1 pack of mouth spray	A selection of the following (up to 4 packs in total): 1 pack of 2 mg lozenges 1 pack of 2 mg gum 1 pack of mouth spray

Box quantities/pieces per box: 25 mg patches—1 box=28 patches; 15 mg patches—1 box=7 patches; gum (4 and 2 mg)—1 box=75 pieces; lozenges (4 and 2 mg)—1 pack=80 lozenges; mouth spray—1 pack=2 mouth sprays.

* Participants will be able to exchange the 2 boxes of 25 mg patches for 8 boxes of 15 mg patches if a lower dose is preferred.

cNRT, combination NRT; NRT, nicotine replacement therapy.

Participants will have the opportunity to select one *Quit Pack* NRT box (see table 1) based on their NRT preferences, including combination NRT options, oral NRT only or patch only (for the second mailing only). The staged delivery of NRT is designed to balance clinical effectiveness, participant autonomy and efficient resource use. Provision of a standardised 8-week baseline supply supports early quit attempts by reducing decision burden at enrolment and ensuring access to evidence-based dosing during the period of highest relapse risk. Each participant will receive a high-dose or low-dose pack, based on their self-reported baseline smoking and vaping behaviours (see figure 1). The follow-up 4-week supply allows participants to select their NRT based on lived experience of cravings, product acceptability and adherence and will be selected by participants during confirmation of additional supply. Dosage of NRT is in line with RACGP guidelines for smoking cessation. In the absence of specific evidence about dosage of NRT for vaping, the same guidelines will be used to support vaping cessation.^36^ Nicotine mouth spray was approved by the Therapeutic Goods Administration in October 2025 for treatment of vaping dependency^36^ and will be included as an NRT option. Participants will have the opportunity to titrate their patch dosage and request 15 mg patches if preferred. *Quit Pack* NRT configurations are informed by data on the most requested NRT types from previous trials,^25^ including the consideration of allowing participants to select lower dosage patches based on their personal preference. As oral NRT is the recommended first-line treatment during pregnancy, participants who are pregnant at enrolment will receive a *Quit Pack* containing oral NRT only. Participants who report low weight (<45 kg) will also only be offered an oral NRT *Quit Pack* box.

Participants will receive an information booklet in their packs which provides: an introduction to the Aboriginal and Torres Strait Islander *Which Way?* team members, including photos, details on how to use the CO monitor (if included in their pack), how to access phone support, how to access and register for the online forum, how to contact the team and a Quit Plan, and an overview of the research process (ie, follow-up time points). The sharing of CO monitor data has been described in a video developed by the *Which Way?* team. The developed *Quit Pack* resources have been designed by and for Aboriginal and Torres Strait Islander peoples and communities, embedding Aboriginal and Torres Strait Islander artwork, ways of knowing, being and doing as central to communicating and translating a range of Indigenous-led educational content and supports. This culturally grounded approach ensures the relevance and responsiveness of all aspects of *Quit Pack* to Aboriginal and Torres Strait Islander peoples and communities, from conception through implementation and beyond.

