### Participant eligibility

Individuals will be eligible to participate if they self-identify as Aboriginal and/or Torres Strait Islander, use cigarettes and/or e-cigarettes (vapes) daily, want to quit and are aged ≥18 years. Pregnant participants will not be excluded from the study. This is consistent with current RACGP guidelines, which state that NRT may be recommended for pregnant women who are unable to quit smoking with behavioural support alone.^35^ Participants who are pregnant at enrolment or become pregnant during the trial will be advised to seek advice from their general practitioner before using NRT. Individuals will be deemed ineligible if they are currently enrolled in any other smoking or vaping cessation programme, self-report a previous allergy or hypersensitivity to nicotine or any ingredient in NRT products, or report experiencing any health condition in the 6 weeks prior to enrolment that is a contraindication for NRT use. This includes heart attack, unstable angina, irregular heart rhythm, stroke/ministroke, brain aneurysm or vascular malformations.

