#### Mailed quit pack, inclusive of NRT

Participants who enrol in *Which Way? Quit Pack* will receive a comprehensive mailed smoking cessation intervention delivered to their nominated postal address. Each *Quit Pack* will include: (1) merchandise from Aboriginal-led, majority Aboriginal-owned accredited social enterprise ‘Clothing the Gaps’ to celebrate pride in culture; (2) a written health education story book developed specifically by the Indigenous *Which Way?* team that offers culturally relevant advice and guidance on quitting and NRT use; (3) an iCOquit Smokerlyzer (for those who report using tobacco only), which is a handheld device that measures CO levels in exhaled breath, supporting self-monitoring and motivation; and (4) a maximum 12-week supply of NRT (see table 1). The *Quit Pack* box and its presentation also embed culturally relevant, engaging and visually meaningful elements throughout, creating an experience that reflects and celebrates Aboriginal and Torres Strait Islander cultures and supports participants to feel culturally represented and safe when receiving and engaging with the intervention. Participants will receive NRT in two separate mailouts. The first will be sent at baseline and will include an 8-week supply of NRT. Six weeks post-enrolment into the intervention, participants will receive an SMS or email (as per their selected preference) asking them to confirm if they wish to receive the further 4-week supply. On confirmation, the second shipment will be mailed (see figure 2). NRT is available over the counter in Australia and does not require a prescription for use.

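### The second NRT mailing is released on the participant's confirmation, with no stated check for pregnancy or a listed cardiac or cerebrovascular event arising after enrolment

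*Protocol article*

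**What the plan says.** Under Participant eligibility, people are excluded if they "report experiencing any health condition in the 6 weeks prior to enrolment that is a contraindication for NRT use". The conditions are then named: "This includes heart attack, unstable angina, irregular heart rhythm, stroke/ministroke, brain aneurysm or vascular malformations". Pregnancy is not an exclusion. The same section says: "Participants who are pregnant at enrolment or become pregnant during the trial will be advised to seek advice from their general practitioner before using NRT".

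Under Mailed quit pack, inclusive of NRT, the supply is split into two mailouts. Eight weeks' worth goes out at baseline. Six weeks after enrolment an SMS or email goes to participants, "asking them to confirm if they wish to receive the further 4-week supply". The release rule follows: "On confirmation, the second shipment will be mailed".

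The text after Table 1 says that participants choose the second supply when they confirm, guided by cravings, acceptability and adherence, and that patch only is an option for this mailing. It also holds the pregnancy rule: "As oral NRT is the recommended first-line treatment during pregnancy, participants who are pregnant at enrolment will receive a" pack with oral products only. Table 1 lists the follow-up menu as patches and/or oral products ("Oral NRT (Participants select up to 4 packs in total" for the oral part), in high-dose and low-dose versions.

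**The concern.** The second mailing is a separate act of supply by the study, six weeks after the only stated health screen. The protocol thought two things worth checking before it first posts NRT: recent cardiac or cerebrovascular events, and pregnancy. Neither is stated to be asked again before more is posted. The oral-only rule is also narrower than its own reason. It rests on what is recommended in pregnancy, yet it is triggered only by pregnancy at enrolment, although Participant eligibility expects that some participants will become pregnant during the trial.

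Followed as written, the process can post patches to someone who became pregnant after enrolment, or more NRT to someone who has since had an event that the protocol itself calls a contraindication. What is at stake is participant safety at low frequency. No effectiveness estimate is affected.

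**Working it through.** There is no stated figure to reproduce. The check sets out the timeline, then the amount of supply, then the possible number of people.

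**Timeline**
- Listed-condition screen: week −6 to week 0 (Participant eligibility).
- Pregnancy trigger for oral-only supply: week 0 (text after Table 1).
- Second-supply message: week 6; release on confirmation (Mailed quit pack).
- Interval with no stated check: weeks 0 to 6.

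**Supply (Table 1; "1 box=28 patches" for 25 mg, 7 per box for 15 mg)**
- Baseline, patch options: 2 × 28 = 56 patches, or 8 × 7 = 56 if exchanged for 15 mg.
- Second mailing: 1 × 28 = 28, or 4 × 7 = 28.
- Left in hand at week w, assuming daily use: 56 − 7w. Week 0: 56; week 3: 35; week 6: 14.
- Share of the remaining patches that a week-6 check could withhold, 28 / (56 − 7w + 28): 28/84 = 33% for a change just after enrolment, 28/63 = 44% at week 3, 28/42 = 67% at week 6.

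These are shares of product, not risks. They show that the check acts on a real part of the supply but cannot recall what is already at home. Advice about the supply in hand must therefore go with it.

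**People**
- Upper bound on unchecked person-time, with all 2000 participants (Sample size) reaching week 6: 2000 × 6/52 = 230.8 person-years.
- Each assumed 1 event per 100 person-years: 230.8 × 0.01 = 2.3 people.
- Listed events, assumed 0.5 to 2 per 100 person-years: 230.8 × 0.005 = 1.2 to 230.8 × 0.02 = 4.6 people.
- The documents give no pregnancy rate or sex split. The same scaling of 2.3 people per 1 per 100 person-years applies to whatever rate is assumed.
- All counts are before removing those who would not ask for a second supply.

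**Look-back**
- With daily use the second supply starts at about week 8. The protocol's own six-week window would then cover weeks 8 − 6 = 2 to 8.
- Under that standard only weeks 2 to 6 of the unchecked interval count: 2000 × 4/52 = 153.8 person-years, or 0.8 to 3.1 listed events at the same assumed rates.
- An event in weeks 0 to 2 would thus not bar the supply by the protocol's own criterion. This argues for a hold with advice, not automatic withdrawal.

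**The case against.** The strongest case against is that this is an absence in a condensed article. The questions on a week-6 form are operational detail, the form is not shown, and neither are the two figures. That stands as a limit: the finding is that no re-check is stated, and a reader should not infer that none will be done. It does not dispose of the point, because the article does more than stay silent. It states what triggers the oral-only rule and what releases the second shipment.

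Second, new pregnancy is addressed. Advice to see a GP before using NRT acts on use, and it reaches the supply already at home. That stands in part. The advice does not change what is posted, the article does not say how a new pregnancy would become known before the mailing, and nothing comparable is stated for a new listed event.

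Third, a reader might infer that women pregnant at enrolment could receive patches at week 6. The text does not support this. The 12-week maximum is listed as part of each pack, so the oral-only rule can be read as covering both mailings for them. Nor does Table 1 help that reading: its baseline rows show no pregnancy or weight restriction either, yet the text imposes both.

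Fourth, NRT is sold over the counter, and a listed-condition screen at enrolment is a normal eligibility criterion. Both are true, and they keep the severity low. The medically supervised support team is an opt-in service and is not described as checking shipments.

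**Conclusion.** The point holds in a limited form and is minor. As stated, the second supply goes out on confirmation alone, and the gap concerns only pregnancy or a listed event arising between enrolment and the week-6 confirmation. The number affected cannot be computed from the documents. It is probably a handful at most, judging by the assumed listed-event rates above and the upper-bound person-time. Sample size, power and the primary estimate do not change.

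Two stronger readings should be resisted. One is that patches are contraindicated in pregnancy: the article calls oral NRT first-line, which does not bar patches. The other is that the sections contradict each other: they do not; the product rule is simply narrower than its stated reason.

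**What to change.** Add two questions to the existing week-6 SMS or email confirmation: is the participant pregnant now, and have they had any of the conditions listed under Participant eligibility since enrolment?

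- **Now pregnant:** offer the oral-only menu, with the GP advice the protocol already provides.
- **New listed event:** hold the shipment and advise the participant to see their GP before using any NRT, including what they still have. Release the shipment once they confirm that they have done so. This gives the doctor who supervises the support team no new role.

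Every recipient of the second supply must already answer this message, so no new contact is needed. The cost is two branching questions, one or two sentences of protocol text, a slight burden on participants and a few delayed shipments. If the confirmation form already asks these questions, no change is needed.

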#### Phone-based behavioural counselling with the *Which Way?* cessation support team

Participants will have access to unlimited phone-based behavioural counselling during business hours (Monday–Friday, 9:00 am–5:00 pm) delivered by one of four Aboriginal and Torres Strait Islander team members (men and women). Team members have completed training through the Nicotine Addiction, Smoking and Vaping Cessation course provided by Avondale University. The *Which Way?* counselling model builds on insights from two previous *Which Way?* trials^25^ and is designed to provide culturally grounded, participant-led support. Participants can opt in to receive behavioural counselling via an information card included in their *Quit Pack,* which will direct them to an online booking system. The cessation support team will deliver tailored guidance on behavioural strategies for smoking and/or vaping cessation and NRT use,^37^ guided by best evidence practice and individual participant needs. The cessation support team will receive ongoing clinical supervision from an Aboriginal medical doctor, with workload management strategies in place to ensure staff well-being and high-quality care.

#### Access to online information and support

All participants will have access to online information and support to assist their quit attempt. Information content will be hosted on the *Which Way?* website and will include educational content and downloadable resources developed specifically by and for Aboriginal and Torres Strait Islander people to support their smoking and vaping cessation journeys. These resources have been codesigned as part of previous trials and include interactive tools to assist with goal setting, tracking progress and staying motivated. Participants will also have access to a secure, password-protected online forum hosted through the existing *Which Way?* website and available as a free downloadable mobile app (available for Apple iOS and Android). The forum provides a space for participants to share experiences and quit stories and connect with others in the programme. The forum will also be used to share health education content, links and videos relevant to smoking and vaping cessation. The forum will be managed by the *Which Way?* team who have received training and education in smoking and vaping cessation and hold or are studying towards tertiary qualifications in social work, medicine and psychology.

### Data collection and measures

Data will be collected between 29 May 2026 and 31 May 2030. Outcome measures and data collection tools have been developed through a series of collaborative workshops with our internal project team, Indigenous investigators and community partners, who have approved our final data collection tools. “It is the powerful influence of the usually invisible standpoints that inform what data are gathered, by whom, and for what purpose” (p 56). In upholding Indigenous quantitative methodologies, the *Which Way?* project acknowledges *“*the extent to which the very categories used to collect statistical information profoundly shape the kinds of interpretations possible” (p 27)*.*^38^

### Outcomes

#### Effectiveness outcomes

*Seven-day point prevalence abstinence*. The primary effectiveness outcome is 7-day point prevalence abstinence, which will be measured at 3, 6 and 12-month follow-ups. This outcome was selected because it minimises recall bias by capturing recent smoking and/or vaping behaviour over a short and clearly defined timeframe. It also aligns with the structure of the intervention, as participants are encouraged, but not required, to set a quit date, and the timing of quit attempts is expected to vary across participants making point prevalence abstinence the most appropriate and comparable outcome. Self-reported 7-day abstinence rates will be assessed in line with recommendations from the Society for Research in Nicotine and Tobacco but modified for the study population.^27^ Seven-day point prevalence abstinence will be derived as answering ‘yes’ to the question, “In the last 7 days, have you stayed smoke and/or vape free (not even a puff)?”. ‘Vape’ will replace ‘smoke’ to assess vaping cessation. Dual cessation will be defined as answering ‘yes’ to both questions.

*Prolonged abstinence* will be measured at 3, 6 and 12 months and defined as continuous abstinence from smoking or vaping from 1 month after receipt of the *Which Way? Quit Pack*, allowing for lapses of up to 7 consecutive days, consistent with established smoking cessation outcome definitions.^39^ Assessment of prolonged abstinence will be restricted to participants who report **7-**day point prevalence abstinence at each follow-up. Participants will be asked, “At any time from 4 weeks after receiving your quit pack, have you smoked for 7 days in a row?”*.* Those who answer ‘no’ will be defined as having achieved prolonged abstinence. Those who answer ‘yes’ will be defined as not achieving prolonged abstinence (had a relapse). Participants who report relapse at any assessment will not be classified as prolonged abstinent at subsequent time points.

*Quit attempts* will be assessed at 3, 6 and 12-month follow-ups. A quit attempt will be defined as a period of intentional abstinence from smoking or vaping lasting longer than 24 hours. At each follow-up time point, quit attempts will be assessed among participants who report ongoing smoking or vaping, or who have relapsed since the previous survey. Participants who report continuous abstinence since the last assessment will not be asked to report quit attempts for that period. At 3 and 6-month follow-ups, participants will be asked, “In the last three months, how many times have you made a quit attempt lasting longer than 24 hours?”, and requested to enter the number of times they have made a quit smoking attempt. At 12-month follow-up, participants will be asked, “In the last six months, how many times have you made a quit attempt lasting longer than 24 hours?”, and requested to enter the number of times they have made a quit smoking attempt.

*Biochemical verification of smoking status*. All participants who reported at baseline who want to quit smoking cigarettes will be invited to undertake biochemical verification of smoking status at 3, 6 and 12-month follow-ups. Verification will be optional and will be conducted using CO breath test via an iCOquit Smokerlyzer, which is provided to participants as part of their *Quit Pack*. The Smokerlyzer connects to an app on the participant’s phone/tablet, enabling participants to self-administer the test. Participants will be asked to submit their CO reading to the research team via text message. This approach enables objective verification of recent smoking status while minimising participant burden and maintaining the remote, community-based nature of the intervention. A cut-point of 6 parts per million will be used to define non-smoking, in line with Society for Research in Nicotine and Tobacco guidelines.^40^ Participants will receive a $20 gift card as reimbursement for the time and effort required to complete each biochemical verification. As biochemical verification of smoking status has not previously been piloted in this intervention setting, data generated through this process will also inform adoption and implementation outcomes, including feasibility, acceptability and participant adherence to verification procedures. These findings will support refinement of verification processes for use in future trials with Aboriginal and Torres Strait Islander people.

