### Statistical analysis

The representativeness of the sample will be assessed by comparing observed proportions to expected proportions derived from Australian Bureau of Statistics population data using χ^2^ goodness-of-fit tests. The RE-AIM quantitative components will be described as counts and percentages with 95% CIs, and qualitative components will be thematically analysed (see table 2). Associations between participant demographic characteristics and quit rates will also be estimated using logistic regression models, as secondary exploratory analyses. Causal machine learning models^31^ will be used to assess potential heterogeneity in effectiveness of implementation strategies by participant subgroups. An ITT analysis will be performed for all effectiveness cessation outcomes, where participants with missing smoking or vaping cessation outcomes are classified as smokers or vapers. Multiple imputation using chained equations will be used to classify all remaining missing outcomes, as well as missing data on confounders. Attrition will be reported in the participant flow chart, and the baseline demographic and smoking/vaping characteristics of completers and non-completers will be compared via t-tests and χ^2^ tests as appropriate. Complete case results will also be reported to provide transparency and allow comparison across analytical methods.^42^ The proportion of participants with a quit attempt longer than 24 hours will be estimated within the subgroup of participants who have not been continuously abstinent at the 3, 6 and 12-month follow-ups.

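### Quit attempts are defined for smoking or vaping, but the entry instruction at 3, 6 and 12 months names quit smoking attempts, so vaping attempts may be missed or recorded inconsistently

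*Protocol article*

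**What the plan says.** Under Effectiveness outcomes, the protocol article defines the outcome for both products: "A quit attempt will be defined as a period of intentional abstinence from smoking or vaping lasting longer than 24 hours". The people asked are likewise users of either product: "quit attempts will be assessed among participants who report ongoing smoking or vaping", together with those who have relapsed since the previous survey. The printed question has no product in it: "how many times have you made a quit attempt lasting longer than 24 hours", with a three-month recall period at 3 and 6 months and a six-month period at 12 months.

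The text then describes the value to be recorded. For the 3 and 6-month surveys, respondents are "requested to enter the number of times they have made a quit smoking attempt. At 12-month follow-up" (the closing words open the next sentence). The same instruction is then given again for the 12-month survey.

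Participant eligibility admits adults who "use cigarettes and/or e-cigarettes (vapes) daily, want to quit and are aged ≥18 years", so the sample can contain smokers, vapers and dual users. Statistical analysis sets the estimand: "The proportion of participants with a quit attempt longer than 24 hours will be estimated within the subgroup of participants". That subgroup is everyone without continuous abstinence at the follow-up concerned, and it is not restricted to smokers.

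**The concern.** The quantity defined and the quantity recorded are not the same. The definition, the people asked and the analysed subgroup all cover vaping, while the recorded number is described in terms of smoking. A vape-only participant therefore belongs to the denominator, but the described entry gives that person no clear way into the numerator.

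The article does state a product-specific version where it intends one. For 7-day abstinence, the word for vaping "will replace ‘smoke’ to assess vaping cessation", and dual cessation needs both answers. Nothing similar is stated for quit attempts.

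Quit attempts are a secondary effectiveness outcome (Study aims; Table 2). The Implementation outcomes text also uses them at 12 months to judge Maintenance, although the Maintenance definition in Study aims and the Maintenance rows of Table 2 do not list them. Attempts that a survey does not record cannot be reliably recovered afterwards.

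**Working it through.** The article prints no figure for this outcome, so there is none to reproduce. The check is a comparison of texts followed by an illustration.

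**Comparison of texts (protocol article)**

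| Element | Section | Products covered |
|---|---|---|
| Eligibility | Participant eligibility | cigarettes, vapes or both |
| Definition of an attempt | Effectiveness outcomes | smoking or vaping |
| Who is asked | Effectiveness outcomes | smoking or vaping |
| Printed question | Effectiveness outcomes | none named |
| Number entered, all three follow-ups | Effectiveness outcomes | smoking |
| Analysed subgroup | Statistical analysis | no restriction |

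Five of the six elements include or allow vaping. Only the entry instruction does not.

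**Who could be affected if the instruction is followed literally**

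- Smoke-only participant: recorded correctly.
- Vape-only participant with an attempt: may enter 0, leave the field blank or count vaping attempts anyway. A blank would appear to fall under the multiple imputation planned for remaining missing outcomes, and its effect cannot be predicted.
- Dual user with at least one smoking attempt: already in the numerator, so the proportion does not change.
- Dual user whose attempts were for vaping only: may be missed.

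**Illustration**

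Let q be the true proportion with an attempt on any product (taken as equal in all groups), v the vape-only share, d the dual-user share, and s the share of attempting dual users who tried to quit vaping only. Shares refer to the analysed subgroup. If everyone affected enters 0:

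observed proportion = q × (1 − v − d × s), and loss = q × (v + d × s).

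All inputs are assumptions; the article gives none of them.

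| v | q = 50%, d = 0 | q = 50%, d = 20%, s = 25% | q = 70%, d = 0 | q = 70%, d = 20%, s = 25% |
|---|---|---|---|---|
| 5% | 47.5% | 45.0% | 66.5% | 63.0% |
| 10% | 45.0% | 42.5% | 63.0% | 59.5% |
| 20% | 40.0% | 37.5% | 56.0% | 52.5% |
| 30% | 35.0% | 32.5% | 49.0% | 45.5% |

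For example, with q = 50%, v = 20% and no dual users, 0.50 × (1 − 0.20) = 0.40, a loss of 10 points. If only half of the vape-only participants enter 0 and the rest count their vaping attempts, the loss is 0.5 × 0.50 × 0.20 = 0.05, or 5 points. If all of them answer the neutral question, the loss is 0.

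**The case against.** The strongest objection is that the question itself, which is the only wording quoted verbatim, names no product. The word smoking appears only in the authors' description of the entry step. The survey form is not shown, the tools are described as final and approved, and product substitution exists elsewhere in the same survey. An article may condense such branching. All of this is fair, and it limits the conclusion: the article establishes a conflict of wording and a risk of miscounting, not a demonstrated bias. It does not remove the conflict, because the article chose to state the definition, the question and the entry, and the third disagrees with the first.

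A reader might go further and infer four things that the article does not support:

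- **Vape-only participants will score zero.** That follows only if they obey the entry description over the question they are asked.
- **The Introduction's prevalences (20% daily smoking, 8.6% current vaping) cap the vape-only share at 8.6 / 28.6 = 30%.** They are population figures, one for daily and one for current use. They do not bound the mix in a self-selected sample of daily users who want to quit.
- **Every vaping attempt by a dual user lowers the result.** The planned analysis is a proportion, so only dual users without any smoking attempt matter. For the number of attempts, the article gives no rule for adding across products.
- **A comparison of smokers with vapers would be distorted.** No such comparison of quit attempts is planned; the logistic models concern demographic characteristics and quit rates.

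**Conclusion.** The inconsistency is real and applies to all three follow-ups. The definition and analysed subgroup cover smoking or vaping, while the described entry covers smoking. If the entry is applied as written, the proportion with an attempt is biased downward by up to the true attempt proportion times the vape-only share, plus a smaller term for dual users who tried to quit vaping only. Under the assumed inputs this runs from 2.5 points (q = 50%, v = 5%, no dual users) to 24.5 points (q = 70%, v = 30%, with the dual-user term). It is zero if participants answer the neutral question. The actual size cannot be stated from the article.

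The point should be corrected because the change is small and the outcome is a reported one. It affects a secondary outcome, also used for Maintenance in one section. The primary outcome, 7-day abstinence at 12 months, is not affected.

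**What to change.** The minimum change is to reword the entry instruction at 3, 6 and 12 months so that it asks for the number of attempts to quit smoking or vaping, in line with the definition.

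The better change is to collect two numbers, attempts to quit smoking and attempts to quit vaping, as the 7-day abstinence item already does by product. Show each entry according to products used at baseline or since. Branching on baseline product alone would miss a smoker who has moved to vaping. Score an attempt on either product as a quit attempt, and report the two counts alongside. A single combined number from a dual user cannot be assigned to a product, even under neutral wording.

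The cost is a wording change and at most one extra item per survey for those shown both entries, with notification of the survey change and agreement from the partners who approved the tools. No visits or participants are added. It is best done before the first 3-month survey goes out. If the live form already asks about both products, only the article's description needs correcting.
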